### Requirement

First, participants will be recruited via an online call through the virtual platforms such as Instagram pages, WhatsApp, and Telegram channel. Candidates will communicate with the trained research assistant (SK; the first author) through the phone number included in the announcement. Then, the research assistant explains the purpose of the study by phone for women who are eligible to enter the study. She will obtain contact information from potential trial participants. The assent will be sent via email or any social media messenger such as Telegram or WhatsApp. Table 1 contains a complete list of the inclusion and exclusion criteria.

**Table 1 Tab1:** Inclusion and exclusion criteria

Inclusion criteria	Exclusion criteria
Women aged 18–49 years Married (having at least one sexual relationship experience) Being the residence of North Iran during the study Tend to participate with informed consent to share information, and participate Women own a smartphone and the ability to use it Women without mental disorders, drug dependence, and addiction	Absence of more than two sessions in training sessions Having a special illness that prevents participants to take part in training sessions Woman who is not interested in the subject of the curriculum

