### Randomization

After informed consent and baseline data collection, participants in the randomized controlled trial will be randomly assigned to the intervention and control arms in a restricted randomized block design. A research identification number will be given to each woman. Then, the identified individuals who volunteered to participate in the study were randomly assigned to the experimental and control groups using a blocking method. Following simple randomization procedures, participants will be assigned to one of the three arms of the trial in a 1:1:1 ratio according to a computer-generated randomization schedule via https://www.sealedenvelope.com/simple-randomiser/v1/lists. The letter A will be considered for the intervention group1, the letter B will be considered for the intervention group2, and the letter C for the control group. The process of random allocation will be continued continuously until the sample size will be reached. Masking of participants and study staff is not possible due to the nature of the intervention (educational) and allocation ratio.

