#### Phase 5: the randomized controlled trial for effectiveness evaluation of the app-based intervention

##### Intervention description

This study is a parallel-group randomized controlled trial. Eligible participants are randomized in a 1:1:1 allocation ratio to one of three groups: two experiment groups, in which women receive the application (app) and digital book. The training contents in both experimental groups outlined preventive behaviors of CC regarding I-Change model constructs retrieved from phases one and two. In another word, group A will be called mobile app group and group B will be called the Digi booklet-group and will receive the same training content in different ways (Fig. 1).

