**Fig. 1 Fig1:**
[figure not shown]
The flow chart of the randomized controlled protocol

Each of the participants in experiment groups A and B will be required to register as a user to download the mobile-App and Digi booklet separately. The educational content will be based on the latest national and international guidelines for the prevention of CC of information (facts).

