##### Control group

Group C as the control group will receive no training content during the study. Following the ethical issue, they only will be provided with educational materials at the end of the intervention procedure. They will receive routine care, such as free health information brochures and free counseling services as needed.

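### The exclusion for missed training sessions can be met only after randomisation and only in arms A and B; applied as written, it would probably bias the comparison with control towards the interventions

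*Protocol article*

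**What the plan says.** The Requirement section introduces Table 1 as exhaustive: "Table 1 contains a complete list of the inclusion and exclusion criteria". The first entry in its exclusion column is "Absence of more than two sessions in training sessions".

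The Randomization section fixes the order of events: "After informed consent and baseline data collection, participants in the randomized controlled trial will be randomly assigned to the intervention and control arms". It also says that participants and study staff cannot be masked.

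Under Intervention description, groups A (app) and B (digital booklet) "will receive the same training content in different ways". The text with Fig. 1 describes delivery by registration and download: each participant in A and B "will be required to register as a user to download the mobile-App and Digi booklet separately". No session schedule appears in the readable text. Table 2 and Fig. 1 themselves are not reproduced in the copy at hand.

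On control, the Control group section says: "Group C as the control group will receive no training content during the study". On teaching material, "they only will be provided with educational materials at the end of the intervention procedure".

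The section on analysis of intervention outcomes mentions a code for missing data. It does not say how women who meet an exclusion criterion after allocation are handled.

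**The concern.** An eligibility criterion should be decidable before allocation and apply equally to every arm. This one does neither. Attendance at training is a consequence of being allocated to A or B, and a control woman has no session to miss.

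The outcomes listed in the article are knowledge, motivation, behavioural intention and preventive action, with Pap smear completion at 3 months named as the basis of evaluation. Women who do not engage with training are plausibly lower on all of these. If they are taken out of A and B while women like them stay in C, the retained intervention women look better than control even when neither intervention works. The Limitation section relies on random allocation to balance participant characteristics in an open trial; this rule would weaken that protection.

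A second difficulty is that a session has no stated meaning for material that a woman downloads. Staff who know the allocation would have to decide what counts as an absence, and could decide differently for the app and the booklet.

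**Working it through.** **Step 1. When and where the rule can act.**

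| Element | Section | Consequence |
|---|---|---|
| Attendance criterion | Requirement, Table 1 | Needs training to have taken place |
| Allocation after consent and baseline | Randomization | Criterion cannot be assessed before allocation |
| Same training content in A and B | Intervention description | Criterion can be met in A and B |
| No training content in C during the study | Control group | Criterion cannot be met in C |

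This step needs no assumption.

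**Step 2. The plan's own sample size.** The article gives 61 per group, two-sided alpha 0.05, power 0.80, 15% dropout and a target of 70 per group (210 in total).

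- 61/(1 − 0.15) = 71.8, and 61 × 1.15 = 70.15. The stated 70 is within two women of either method, and 3 × 70 = 210.
- The means and SDs behind the 61 are not given. With equal SDs it implies a detectable standardised difference of (1.960 + 0.842) × √(2/61) = 0.507.
- After 15% dropout, 70 × 0.85 = 59.5, so about 60 per group is used below.

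**Step 3. Bias on a continuous score when there is no true effect.** Let f be the share of an intervention arm removed and g the deficit of removed women against retained women, in SD. The whole arm has mean (retained mean − f × g). With no effect, control has the same mean as the whole arm, so retained women exceed control by f × g.

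Assumed ranges, not from the documents: f = 10%–30%, g = 0.5–0.8 SD. With 60 controls and 60(1 − f) intervention women, the standard error is √(1/[60(1 − f)] + 1/60), k = f × g / SE, and two-sided rejection at 0.05 is 1 − Φ(1.96 − k) + Φ(−1.96 − k).

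| f | g (SD) | Bias (SD) | n retained | SE | k | Type I error |
|---|---|---|---|---|---|---|
| 10% | 0.5 | 0.05 | 54 | 0.188 | 0.27 | 0.058 |
| 10% | 0.8 | 0.08 | 54 | 0.188 | 0.43 | 0.071 |
| 30% | 0.5 | 0.15 | 42 | 0.201 | 0.75 | 0.116 |
| 30% | 0.8 | 0.24 | 42 | 0.201 | 1.19 | 0.222 |
| either | 0 | 0 | 54 or 42 | – | 0 | 0.050 |

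Against the detectable 0.507 SD, the bias is 0.05/0.507 = 10% to 0.24/0.507 = 47%.

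**Step 4. The same check for Pap smear completion.** Let p be the completion rate in every arm with no effect, and suppose removed women complete at half that rate (assumed). Retained women then complete at (p − 0.5 f p)/(1 − f). For p, take the lowest and highest Iranian participation rates quoted in the Background, 27.1% and 58.6%. These are not 3-month completion rates and serve only as a range. Here n = 70 controls and 70(1 − f) intervention women.

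| p | f | Retained rate | Spurious difference | Type I error |
|---|---|---|---|---|
| 27.1% | 15% | 29.5% | 2.4 points | 0.060 |
| 27.1% | 30% | 32.9% | 5.8 points | 0.104 |
| 58.6% | 15% | 63.8% | 5.2 points | 0.093 |
| 58.6% | 30% | 71.2% | 12.6 points | 0.300 |

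As with the scores, if removed women complete at the same rate as the rest, the difference is zero.

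**The case against.** The strongest reply is that the article never says that excluded women leave the analysis. Table 1 lists the criterion, but no sentence stops their follow-up or drops their data. The analysis set is commonly defined in a full protocol or analysis plan that is not shown, and the article commits to CONSORT reporting. This stands as a qualification: the bias is conditional on removal. It does not clear the line. Removal is the natural meaning of an exclusion criterion, nothing in the article offsets it, and an analysis plan that kept these women would contradict Table 1.

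A second reply is that, if the intervention has no sessions, nobody can be absent and the rule is idle. A reader might go further and infer that the intervention certainly has none. The documents do not support that, because the schedule and flow chart are not reproduced. What can be said is that the readable text does not define a session. Either the rule has no meaning or it acts on A and B alone, and the wording needs correction in both cases.

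A third reply is that the size is entirely assumed. That is correct. At the low end the type I error is 5.8%, which is negligible, and with no difference between removed and retained women there is no bias.

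A reader might also infer that the rule uses up sample beyond the 15% dropout allowance. The sample size section does not define dropout, so these women may be exactly what the allowance covers. Nor does anything show that the other two exclusion criteria, special illness and lack of interest, are applied after allocation; both can be judged at screening.

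**Conclusion.** The concern holds in conditional form. It is certain from the text that the attendance criterion can be met only after randomisation and only in arms A and B. If it is applied as written and the excluded women leave follow-up or analysis, the comparison of each intervention with control is no longer the randomised one. The bias would probably favour the interventions; that direction is a judgement about less engaged women, not something the documents state.

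The size is unknown. Under the assumed 10–30% removal and 0.5–0.8 SD deficit, the bias is 0.05–0.24 SD and the type I error about 6%–22%. With no deficit there is only loss of sample. The app-versus-booklet comparison is affected only if the rule removes women differently in the two arms, which an undefined session and unmasked staff leave open.

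The line should be corrected before the analysis because it bears on every comparison with control, and follow-up that is not collected cannot readily be recovered.

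**What to change.** - Delete the missed-sessions line from the exclusion criteria in Table 1.
- State that all randomised women are followed up and analysed in the arm to which they were allocated, whatever their use of the app or booklet.
- Report use as an adherence measure, defined separately for the app and the booklet. Any per-protocol analysis should be labelled supportive only.
- As a clarification, state that the other two exclusion criteria are assessed at screening, before randomisation.

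This is a change of wording that the article's provision for protocol amendments can carry, and the target stays at 70 per group. The cost is that the estimated effect may be slightly smaller, because women who do not use the material remain in the comparison.

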### Randomization

After informed consent and baseline data collection, participants in the randomized controlled trial will be randomly assigned to the intervention and control arms in a restricted randomized block design. A research identification number will be given to each woman. Then, the identified individuals who volunteered to participate in the study were randomly assigned to the experimental and control groups using a blocking method. Following simple randomization procedures, participants will be assigned to one of the three arms of the trial in a 1:1:1 ratio according to a computer-generated randomization schedule via https://www.sealedenvelope.com/simple-randomiser/v1/lists. The letter A will be considered for the intervention group1, the letter B will be considered for the intervention group2, and the letter C for the control group. The process of random allocation will be continued continuously until the sample size will be reached. Masking of participants and study staff is not possible due to the nature of the intervention (educational) and allocation ratio.

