### Outcome measures

The initial research questions addressed in this study are “Does the educational intervention based on the I-Change model via mobile app affect CC preventive behaviors among Iranian women?”. To answer this main question, the following primary outcomes are expected:Determining and comparing the effects of an educational intervention designed based on the I-Change model via a mobile app knowledge related to CC prevention in women in the target and control groups before, immediately, and 3 months after the interventions.Determining and comparing the effects of an educational intervention designed based on the I-Change model via a mobile app on information factors related to CC prevention in women in the target and control groups before, immediately, and 3 months after the interventions.Determining and comparing the effects of an educational intervention designed based on the I-Change model via a mobile app motivation to CC prevention in women in the target and control groups before, immediately, and 3 months after the interventions.Determining and comparing the effects of an educational intervention designed based on the I-Change model via a mobile app predisposing factors to CC prevention in women in the target and control groups before, immediately, and 3 months after the interventions.Determining and comparing the effects of an educational intervention designed based on the I-Change model via a mobile app behavioral intention to CC prevention in women in the target and control groups before, immediately, and 3 months after the interventions.Determining and comparing the effects of an educational intervention designed based on the I-Change model via a mobile app action to prevent for CC prevention in women in the target and control groups before, immediately, and 3 months after the interventions.

Consequently, we expect the effect of our educational intervention on preventive action regarding CC among women. To assess the expected secondary outcomes, a self-reported assessment addressing preventive actions (using a condom, doing pap-test and genital examination) will be conducted.

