#### Phase 5: analysis of intervention outcomes

To ensure that the data is correctly entered, a double-entry of data will be performed by two different individuals. All data obtained from women will be entered into SPSS software. A code will be defined to identify missing data. The obtained data will be kept strictly confidential and will be stored with secured and restricted access; also, the signed consent will be kept locked. Follow-up data are received using the same questionnaires as used at baseline. The intervention will be evaluated based only on Pap smear completion 3 months after the enrollment and baseline survey. Data will be summarized with descriptive statistics (mean, median, standard deviation, percentiles for numerical variables, frequencies, and percentages for categorical variables). To determine the normality of data, Smirnov and Kolmogorov will be used. Determining the frequency of demographic information in both groups is analyzed using descriptive statistics templates. To analyze the quantitative variables, the independent *t*-test and paired *t*-test are analyzed. To compare the mean score, the quantitative (intra-group) variables of the two groups of the test and control groups before and after the intervention were used as independent samples. To compare the means, the quantitative (inter-group) variables were compared between the two groups of control and test before and after paired *t*-test intervention is used. In the case of non-normalization, the mean score of the quantitative (intra-group) variables in the two groups of the test and control groups is used before and after the intervention in Mann-Whitney. To compare the meanings, the quantitative variables (inter-group) were used in both control and test groups before and after the Wilcoxon test. To determine the relationship between the underlying and dependent variables in the case of normal, the Pierson correlation test is used and the Spearman correlation test will be used to determine the relationship between the underlying and dependent variables in the case of normal. To analyze the qualitative variables, a chi-square test is used to analyze the qualitative variables. The significance level in this study is considered to be 0.5. The information obtained will be used by the related statistical software, including SPSS version 23.

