## Limitation

Our study may face several limitations. As it is an open study and participants are aware that they are entering into an intervention entitled in cervical cancer prevention behaviors, bias is likely in the study results. Then, a random allocation of participants can help achieve a balance in sociodemographic characteristics. Another limitation of this study is the need to use self-reporting tools, and the possibility of memory error, lack of clarity, socio-cultural concerns, and individual biases affecting the results are inevitable. Last but not least, our study may have dropouts during the enrolment phase of the CONSORT process because some participants might not have access to a smartphone and the time extension for enrollment to achieve the estimated sample size is probable.

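### The protocol wrongly says that the teaching content and the allocation ratio make it impossible to mask study staff; data entry and analysis could be masked, although most of the open-label bias would remain

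*Protocol article*

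**What the plan says.** The Randomization section gives the rule and its reasons in one sentence: "Masking of participants and study staff is not possible due to the nature of the intervention (educational) and allocation ratio". It makes no exception for any group of staff, and no other section provides for masking anyone.

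The same section says that "participants will be assigned to one of the three arms of the trial in a 1:1:1 ratio". It labels the arms openly by letter: A and B for the two intervention arms, C for control. It also says: "A research identification number will be given to each woman".

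On data collection, the Outcome measures section says that "a self-reported assessment addressing preventive actions (using a condom, doing pap-test and genital examination) will be conducted". The Phase 5 analysis section adds "Follow-up data are received using the same questionnaires as used at baseline", and says that "a double-entry of data will be performed by two different individuals". It then describes a normality check (Kolmogorov-Smirnov) that leads to t-tests or, failing normality, to Mann-Whitney and Wilcoxon tests.

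The Limitation section calls the study open and accepts that "bias is likely in the study results". In its full context that sentence refers to the participants' awareness of the intervention. The response it offers is random allocation, to balance sociodemographic characteristics.

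**The concern.** The article does more than leave masking undescribed. It states that masking staff is impossible and gives two reasons. If the reasons are wrong, a protection that the trial could have is ruled out on a false ground.

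The outcomes are questionnaire scores for knowledge, motivation, intention and related constructs, plus reported preventive actions, so there are few hard endpoints to anchor the result. Someone who knows the arm may follow women up differently, resolve unclear entries differently, or settle the choice of test after seeing which result favours the app. Randomisation balances the arms at baseline and does not protect any of these later steps.

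**Working it through.** No figure in the protocol depends on this sentence, so the check sets its two reasons against each group of people involved.

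**Reason 1: the allocation ratio.** The ratio is 1:1:1. A ratio sets arm sizes and does not tell anyone which arm a given woman is in. With equal arms, even the counts per coded arm do not identify the arm. This reason holds for nobody.

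**Reason 2: the educational intervention.**

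| Group | Does the content reveal the arm? | Basis in the protocol article |
|---|---|---|
| Women | Yes | Each registers for the app or the booklet, or receives no training content (Phase 5, Control group) |
| Staff giving access to app or booklet | Yes | They handle the material itself |
| Staff sending or receiving follow-up questionnaires | Not necessarily | Same questionnaires as at baseline; mode of completion not stated |
| The two data-entry persons | No | They can work from a questionnaire carrying a research number |
| Analyst | No | Can work from re-coded arm labels |

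The second reason therefore holds for the first two groups only.

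**Are the means available?** Research numbers and letter codes for the arms are already planned. The meaning of A, B and C is published in the article, so those letters mask nothing and the labels would need re-coding.

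**How much of the bias could masking remove?**
- Self-report by women who know their arm: not removable this way. The respondent is in effect the assessor.
- Follow-up contact: removable to the extent that contact would otherwise differ by arm. The article does not say whether questionnaires are self-completed or administered by staff.
- Data entry: removable, but double entry already limits it.
- Analysis: removable. The tests are chosen from the data, and the arm labels need not be known when that choice is made.

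**Illustration under assumed bias sizes.** Take 61 women per group (Sample size section), a two-sided 0.05 level, the normal approximation and no true effect. The standard error of a difference in SD units is √(2/61) = 0.181. For a differential bias of b SD, the chance of a significant result is 1 − Φ(1.96 − b/0.181) + Φ(−1.96 − b/0.181).

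| Assumed b (SD) | Chance of a significant result |
|---|---|
| 0 | 5% |
| 0.05 | 5.9% |
| 0.10 | 8.6% |
| 0.20 | 19.7% |
| 0.30 | 38.1% |

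The values of b are assumptions. The document supports none of them and does not show what share of any such bias would come from staff. The table shows only that small differential errors matter at this sample size; it does not estimate the bias in this trial.

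**The case against.** The strongest reply is that the sentence stands in a paragraph on allocation and may be meant only for those who allocate and deliver. On that view, masking of data entry and analysis is detail that a journal article leaves to a fuller document. Silence alone would indeed be no finding. But the article is not silent: it says that staff cannot be masked, without exception, and one of its reasons is wrong for everyone.

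Three stronger readings are tempting, and the document does not support them.

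- **That unmasked assessors will bias the outcomes.** No section says that staff interview women at follow-up. The interviews described belong to the qualitative work and app development. With self-report, the main source of bias is the woman herself.
- **That the protocol admits staff bias.** The Limitation section ties the likely bias to participants' awareness and concedes nothing about staff or the analyst.
- **That masking costs nothing because separate data-entry persons already exist.** The Phase 5 analysis section says only that the two differ from each other. They might also recruit or give access.

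It is also fair to say that the choice of test follows a named normality check and is not left to free judgement. What stands against this is that the choice is still made from the data. The article does not say at what level, or on which variables and arms, the check is applied, so some discretion remains.

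**Conclusion.** The concern holds in a limited form. The stated rationale is wrong: a 1:1:1 ratio prevents no masking, and the educational content unmasks only participants and those who give access. Masking data entry and analysis is feasible with what the plan already contains.

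Most of the open-label bias will remain whatever is done, because unmasked women report their own outcomes. The avoidable part lies in follow-up contact, data entry and analysis. It is probably modest if questionnaires are self-completed and larger if staff administer them. The document does not say which, so the size cannot be derived. The correction is still worth making: the error is plain, the remedy is cheap, and the analysis has a data-dependent step that masking would protect.

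**What to change.** In the Randomization section:

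1. Delete the allocation ratio as a reason against masking.
2. State that participants, and the staff who give access to the app or booklet, are not masked.
3. State that the same follow-up questionnaire is sent in the same way to all three arms.
4. State that data entry and analysis use research numbers and re-coded arm labels (not the published A, B and C), with the key withheld until the database is locked and the choice of tests is fixed.

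In the Limitation section, say that self-report by unmasked women remains a source of bias that these steps do not remove.

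The cost is a change of wording and a small constraint on roles. A team member other than the analyst must hold the key, and those entering data should not be those who give access. In a small team this may mean reassigning a task. No change to sample size, visits or outcomes is needed.
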